## Abstract

**Background:**

Patient and public involvement and engagement (PPIE) in research is a collaboration between researchers, patients, and the public, enhancing research acceptability, relevance, and impact. There is a growing prevalence of PPIE in high-income country research; however, its integration in low- and middle-income countries (LMICs) remains poorly understood. Recognising this gap, the Ziauddin University Clinical Trials Unit in Karachi, Pakistan, launched a dedicated PPIE initiative in 2022. This study evaluates the engagement process and experiences of patient and public members and researchers to identify barriers and facilitators to participation within the PPIE group.

**Methods:**

The evaluation uses an explanatory sequential mixed-method design. First, the Public and Patient Engagement Evaluation Tool (PPEET) questionnaire will be administered online to group members, coordinators, and senior institutional leads. Insights from questionnaires will be further explored during semi-structured interviews, with questions guided by the Patient Engagement in Research (PEIR) framework, supplemented with analysis of project documentation. Study activities will be conducted in both English and Urdu. The study has been co-designed with PPIE members and is co-led with a public partner. Findings will highlight areas for improvement, inform best practices, and guide the development of more effective engagement strategies.

**Outcome:**

Although focused on a single group, this evaluation lays the groundwork for understanding PPIE practices in LMIC contexts. It provides valuable insights into developing equitable partnerships and improving patient-centred research. This study contributes to a growing body of knowledge, offering practical guidance for implementing PPIE in settings with unique socioeconomic challenges and cultural realities. The findings are expected to benefit the local research community and similar initiatives globally, particularly in regions with comparable challenges.

## Introduction

Patient and public involvement and engagement (PPIE) represents a paradigm shift in research by empowering communities to actively shape the generation of evidence in healthcare. The National Institute for Health and Care Research (NIHR) defines it as conducting research “with” or “by” the public, rather than “to”, “about” or “for” them
^
1,
2
^. By actively involving patients and public partners, and integrating their perspectives, PPIE enhances the relevance, acceptability, and impact of research, aligning it more closely with real-world needs and priorities
^
3–
6
^. Studies have shown that PPIE delivers ethical and practical benefits, such as influencing study design, improving recruitment by aligning practices with patient needs, guiding dissemination and ensuring greater accessibility of findings to the public
^
7–
9
^.

While PPIE has become increasingly established in high-research output countries such as Australia, Canada, New Zealand, the United Kingdom and the United States, its adoption in low- and middle-income countries (LMICs) remains limited
^
10–
13
^. A 2022 scoping review found that only one of 33 studies evaluating PPIE processes was conducted in an LMIC
^
14
^. Reviewing engagement processes in these settings is essential, as lessons from high-income countries (HICs) may not directly apply to these contexts marked by structural inequities, social hierarchies, and limited public trust in research
^
15
^. Furthermore, engagement in LMICs often relies on community leaders or gatekeepers, whose perspectives may not represent the wider community. These challenges are further compounded by social exclusion, gender inequities, and limited access to healthcare
^
16
^.

Recognising this gap, the Ziauddin University Clinical Trials Unit (CTU) in Karachi launched Pakistan’s first dedicated PPIE group in 2023, supported by an engagement bursary
^
17
^. The initiative aimed to embed PPIE within research infrastructure and create a structured platform for community input into study design and review. Using tools such as the ‘My Involvement Profile’ template helped clarify members’ expectations, foster trust, and identify practical strategies for collaboration between researchers and local communities in a resource-limited context
^
17
^.

During its first year, the group reviewed informed-consent processes, proposed improvements to public-facing materials, and developed mechanisms for sharing trial results with the wider community. It has also contributed to major international clinical trials, including REMAP-CAP (Randomised, Embedded, Multifactorial, Adaptive Platform trial for Community-Acquired Pneumonia) and Mega-ROX (Mega Randomised Registry Trial Comparing Conservative vs. Liberal Oxygenation Targets). Membership has evolved over time, reflecting the challenges of sustaining long-term involvement, although these changes have not affected the project’s overall outcomes.

Research is often less prominent and less favourably perceived by the public in many LMICs compared to HICs, making engagement more challenging and necessitating different approaches
^
18,
19
^. Unfortunately, there are no best practice guidelines for PPIE in LMICs due to limited published experiences and a lack of research evaluating effective engagement methods. Accordingly, there is an urgent need to explore and develop strategies tailored to meet these realities
^
7
^.

In line with NIHR guidance, this paper uses the term “patient and public involvement and engagement (PPIE) to describe our work. “Involvement” refers to patients and public partners actively contributing to the research process (e.g. design, review of consent materials, dissemination); while “engagement” refers to researchers sharing information and research findings with the public. Our group primarily promotes involvement while also supporting engagement through public-facing activities.

To our knowledge, very few published studies from Pakistan explicitly describe patient or public involvement in research. This study aims to evaluate the engagement processes within the PPIE group, explore the experiences of its members, coordinators, and senior institutional leads, and identify barriers and facilitators to effective engagement. By addressing these objectives, the study contributes to the evidence base for PPIE practices in LMICs.

## Methods

### Study design & setting

The study employs an explanatory sequential mixed-method design combining quantitative and qualitative methodologies to evaluate patient and public engagement within the PPIE initiative
^
2,
20–
23
^. Guided by the participatory action research approach, the study was co-designed with PPIE group members to ensure relevance, inclusivity and alignment with their needs and expectations. In the first phase the validated Public and Patient Engagement Evaluation Tool (PPEET) questionnaire will be administered to identify broad patterns of experience
^
2
^. Results will then inform the qulitaitve phase, which includes semi-structured interviews and a review of project documentation. Equal weighting is given to both methods which together provide measurable indicators and contextual understanding of engagement quality, offering a comprehensive view of engagement efforts. Findings will be reported using the Guidance for Reporting Involvement of Patients and the Public 2 (GRIPP2) checklist
^
24
^.

### Study participants

Study participants include current (n=6) and past (n=3) members of the PPIE group, representing both patient and public representatives, as well as the PPIE coordinators (n=3) involved in establishing the group. Two senior institutional leads, including a department head and a CTU board representative, will be asked to share their experiences overseeing and integrating PPIE efforts into institutional practices and priorities. This sample (n=14) represents the full population of individuals directly involved since the inception of the initiative, making it exhaustive rather than sampled. The process evaluation aims to provide an in-depth understanding of engagement within this institutional setting, rather than achieve generalisability.

### Recruitment

Current PPIE members and coordinators will be introduced to the study during a regular PPIE group meeting or via WhatsApp if unable to attend. Senior institutional leads and past members will be contacted via email. All potential participants will receive the participant information sheet (PIS) in their preferred language (either English or Urdu), outlining the study’s purpose, procedures, and confidentiality measures. Potential participants will have opportunities to ask clarifying questions in person, via WhatsApp or through email. Participants will be given a two-week window to complete the questionnaire, with reminders issued by the study lead after one week and two days before the deadline. Following this, all participants will be invited to participate in semi-structured interviews, regardless of whether they completed the questionnaire. The PIS will be re-shared at this stage.

All invitations will be made by the study co-leads who do not hold a hierarchical relationship with participants, to minimise any perceived pressure or undue influence.

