Demographic data, such as age, sex, education, ethnicity, and professional status, will not be collected through the questionnaire in order to ensure anonymity. Instead, demographic information previously recorded as part of routine project documentation will be reported. To ensure accessibility, the questionnaire will be translated into Urdu. The translation will be confirmed by the PI and co-PI, who are fluent in both English and Urdu. Prior to distribution, the translated version will be piloted for coherence. Additionally, the PPIE co-lead will be available to clarify terminology or content as needed.

All survey data will be handled and stored confidentially as detailed in the Data Analysis & Management section.

**
*Semi-structured Interviews.*
** All participants will be invited to participate in semi-structured interviews lasting 30–60 minutes, at the university or their preferred location, conducted in English or Urdu based on their preferences. The interview guides are aligned with the Patient Engagement in Research (PEIR) framework
^
25
^ to explore the perceived benefits of engagement, challenges faced, and opportunities for improvement. Insights from the questionnaire will inform and refine the interview questions. The interview guide for senior institutional leads has been adapted to focus on organisational-level considerations using the PPEET domains, such as policies and strategies for PPIE, as the PEIR framework is not tailored to this context. Interviews will be audio-recorded, transcribed verbatim, and translated into English if conducted in Urdu. Participants will have the opportunity to review and verify their transcripts to ensure accuracy.

The study lead and PPIE Coordinator (AH) will primarily interview researchers, while the co-lead and PPIE member (MK) will focus on interviewing PPIE members to manage any potential power imbalances during the interviews. While one facilitates the interview, the co-lead will observe to ensure consistency and capture additional thoughts. Both leads will interview each other first to mitigate bias in subsequent interviews, and this paired interviewer approach aims to create an open environment for participants to share both positive and critical reflections, particularly regarding power dynamics or institutional challenges.

**
*Project documentation.*
** A review of project documentation will be conducted to triangulate findings from interviews and questionnaires
^
2

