### Study timeline & management

The project will run from September 2024 to February 2025. Ethics applications were submitted in July 2024. The PPEET questionnaire will be administered in September and subsequent interviews will be completed by November 2024. Data analysis will be completed by January 2025. The study is led collaboratively by a public partner (MK) and one of the PPIE coordinators (AH), with input from a steering group consisting of other PPIE coordinators (NA, TT) and senior researchers (SM, AMD, MH) associated with the overall PPIE project that brings extensive research experience to ensure appropriateness of study procedures. Authors AH, MK, NA and MH also provide local expertise to ensure the study’s relevance and appropriateness for the Karachi context and oversee local ethical approvals.

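### The assurance that the inviting co-leads stand in no hierarchy to participants is unsupported for the study lead, who is a coordinator of the evaluated group and sends both reminders to members

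*Protocol article*

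**What the plan says.** All references are to the protocol article.

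- **Recruitment** makes one statement about both inviters: "All invitations will be made by the study co-leads who do not hold a hierarchical relationship with participants, to minimise any perceived pressure or undue" [...]. The stated purpose is to keep perceived pressure low.
- **Recruitment** also gives participants two weeks to complete the questionnaire, "with reminders issued by the study lead after one week and two days before the deadline".
- **Data collection (Semi-structured Interviews)** identifies one co-lead as "The study lead and PPIE Coordinator" and describes the other as a PPIE member. The first mainly interviews researchers and the second concentrates on members, so that possible imbalances of power are managed.
- **Study timeline & management** confirms the pairing: "The study is led collaboratively by a public partner" together with one of the coordinators.
- **Study participants** lists "the PPIE coordinators (n=3) involved in establishing the group", 6 current and 3 past members, and two senior institutional leads, who "will be asked to share their experiences overseeing and integrating PPIE efforts into institutional practices and priorities".

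**The concern.** The sentence in Recruitment describes both co-leads at once, but the two hold different positions in the project being evaluated. One is a member among members. The other is a coordinator, and the coordinators took part in setting up the group.

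The article treats that difference as worth managing at the interview. At the invitation and reminder step it describes the same person as free of hierarchy. The reminder step is the more exposed of the two, because only the study lead is named as the sender and members are not exempted.

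Two things are at stake. First, a member deciding whether to take part, or how critically to speak, may feel some pressure when a coordinator asks and then follows up twice. Members' experience is central to what the evaluation wants to learn. Second, the final report could repeat an assurance about voluntariness that the article's own role descriptions do not support.

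**Working it through.** The question is mainly one of consistency between sections, with a short count to size it.

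**Step 1. Reproduce the stated total.** Study participants gives 6 current members, 3 past members, 3 coordinators and 2 senior leads. 6 + 3 + 3 + 2 = 14, which matches the article.

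**Step 2. Set the role statements side by side.**

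| Step | Who acts towards members | What the article says of that person |
|---|---|---|
| Invitation (Recruitment) | Both co-leads, no split by group stated | No hierarchical relationship with participants |
| Questionnaire reminders (Recruitment) | Study lead, 2 of 2 reminders | Covered only by the same sentence |
| Interview (Data collection) | Mainly the public co-lead, with the other co-lead observing | Split by role to manage possible power imbalances |

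The interview row recognises a possible gradient between researchers and members. The first two rows do not take it into account for the same study lead. One could read the invitation sentence as meaning that each person is invited by whichever co-lead is suitable. The reminders would still come from the study lead.

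**Step 3. Count the invitees for whom the assurance is in doubt.** The Discussion says that both co-leads are themselves planned participants, so both are removed from the count of people who could feel pressure.

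- Other invitees: 14 − 2 = 12.
- Coordinators other than the study lead: 3 − 1 = 2. They share the study lead's role.
- Senior leads: 2. Any hierarchy here runs upward from the study lead.
- Members other than the public co-lead, assuming that person is one of the 9: 9 − 1 = 8.
- Check: 8 + 2 + 2 = 12.
- Share: 8 / 12 = 67%.

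The assumption matters little. If the public co-lead were not among the 9 members, only the study lead would be removed from the 14, giving 9 of 13 = 69%.

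The 8 is a ceiling. It includes past members, who have left the group and for whom a coordinator's standing may matter less. The documents do not allow the count to be refined further.

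**The case against.** The strongest reply is that role is not hierarchy. The article says that coordinators helped to establish the group. It nowhere says that the study lead has authority over members. The remark on power imbalances is conditional and concerns interviews. An informal difference of standing can exist without a hierarchical relationship, so the two sections do not strictly contradict each other. This stands, and it is why the assurance is called unsupported for the study lead and not false. It does not remove the point, because the sentence aims at perceived pressure, which needs no line of command.

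The second reply is that other protections are in place. Under Informed consent the questionnaire can be answered anonymously. Under Ethics and consent the survey opens with a choice to decline that ends it at once, and interviews need separate written consent. The information sheet is given again before interviews, and members are mainly interviewed by a fellow member. These limit the harm considerably, above all for the questionnaire, which is what the reminders concern. They do less for the decision to be interviewed, since the co-leads conduct and observe the interviews and will know who took part.

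The third reply is that the coordinator role is already disclosed elsewhere, and that the Discussion admits possible response bias and brings in non-participant senior researchers. That is true, but their task is interpretation, which comes after the decision to take part.

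A reader might go further and add the two senior leads to all 9 members, concluding that the assurance fails for 11 of 14 invitees (79%). The documents do not support this. That count includes the public co-lead, who is one of the inviters. It also includes the senior leads, who oversee the PPIE work. Whether they oversee the study lead personally is an inference, and a more junior person inviting a department head puts no downward pressure on that invitee. At most this bears on the literal accuracy of the sentence.

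**Conclusion.** The point holds in a limited form. The blanket assurance is not supported for the study lead in relation to members, who are at most 8 of the 12 invitees other than the co-leads (67%). The count rests on the public co-lead being one of the 9 members. The assurance is not contradicted for the public co-lead, so the safeguard is partly intact.

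A reader might infer that there is no safeguard against undue influence, or that participation and answers will be biased towards courtesy. Neither follows. The documents show a difference of role without formal authority, one of the two inviters is a peer of the members, and the size of any effect on participation or candour cannot be derived from what is given. No sample count, summary or analysis changes. The change is still worth making, because it concerns the group whose experience matters most to the evaluation and costs almost nothing.

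**What to change.** 1. Extend the interview role split to recruitment. The public co-lead sends invitations and both questionnaire reminders to current and past members. The study lead may contact the coordinators and senior leads.
2. Rewrite the sentence in Recruitment so that it claims for each co-lead only what is true of that person. For example: members are invited and reminded by the public co-lead, who is a fellow member; the other co-lead is a coordinator of the group and contacts only coordinators and senior leads.
3. If contacts have already been made, correct the sentence and report which co-lead invited and reminded which group.

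**Cost.** A wording change and a different sender for one group. If messages go out individually, the public co-lead sends at most 8 × 4 = 32 short messages: a questionnaire invitation, two reminders and an interview invitation for each of 8 members. No new staff are needed, and data collection and analysis are unchanged.

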### Data collection

The study involves three key components for data collection: a validated questionnaire, semi-structured interviews, and project documentation review.

**
*Public and Patient Engagement Evaluation Tool (PPEET).*
** The PPEET questionnaire, a widely used and validated tool developed by researchers at McMaster University, will be used to assess engagement effectiveness on a series of Likert scale items
^
2
^. Participants will respond to statements on a 5-point Likert scale ranging from “Strongly disagree” to “Strongly agree,” with optional free-text fields allowing respondents to expand on their experiences.

The questionnaire will be administered through an online survey tool (Google Forms) in September 2024, 18 months after the researchers started the PPIE project and one year after the first meeting of the PPIE group.

The PPEET is divided into three questionnaires tailored for different stakeholders: project participants, project coordinators, and organisational leads. These assess experiences and involvement at individual, project, and institutional levels, respectively, while providing valuable insights into the broader PPIE initiative. Responses from the survey will be used to identify areas for deeper exploration during interviews, e.g. lower scores in domains such as “impact and influence” will guide follow-up questions to understand underlying reasons.

*Participant Questionnaire* will employ Module B, focused on long-term engagement. The questionnaire comprises 22 questions addressing four key domains: communication and support for participation, opportunities for sharing views, impact and influence of the engagement process, and general reflections.

*Project Questionnaire* includes three modules designed to evaluate different phases of engagement: planning (Module A), implementation (Module B), and impact assessment (Module C). All three modules will be completed by the PPIE coordinators.

*Organisation Questionnaire* evaluates institutional engagement practices, providing insights into policies, participatory culture, collaboration, impact assessment, and organisational reflections. It is designed to identify trends, document improvements, and facilitate audits. This questionnaire will be completed by both senior institutional leads.

Demographic data, such as age, sex, education, ethnicity, and professional status, will not be collected through the questionnaire in order to ensure anonymity. Instead, demographic information previously recorded as part of routine project documentation will be reported. To ensure accessibility, the questionnaire will be translated into Urdu. The translation will be confirmed by the PI and co-PI, who are fluent in both English and Urdu. Prior to distribution, the translated version will be piloted for coherence. Additionally, the PPIE co-lead will be available to clarify terminology or content as needed.

All survey data will be handled and stored confidentially as detailed in the Data Analysis & Management section.

**
*Semi-structured Interviews.*
** All participants will be invited to participate in semi-structured interviews lasting 30–60 minutes, at the university or their preferred location, conducted in English or Urdu based on their preferences. The interview guides are aligned with the Patient Engagement in Research (PEIR) framework
^
25
^ to explore the perceived benefits of engagement, challenges faced, and opportunities for improvement. Insights from the questionnaire will inform and refine the interview questions. The interview guide for senior institutional leads has been adapted to focus on organisational-level considerations using the PPEET domains, such as policies and strategies for PPIE, as the PEIR framework is not tailored to this context. Interviews will be audio-recorded, transcribed verbatim, and translated into English if conducted in Urdu. Participants will have the opportunity to review and verify their transcripts to ensure accuracy.

The study lead and PPIE Coordinator (AH) will primarily interview researchers, while the co-lead and PPIE member (MK) will focus on interviewing PPIE members to manage any potential power imbalances during the interviews. While one facilitates the interview, the co-lead will observe to ensure consistency and capture additional thoughts. Both leads will interview each other first to mitigate bias in subsequent interviews, and this paired interviewer approach aims to create an open environment for participants to share both positive and critical reflections, particularly regarding power dynamics or institutional challenges.

**
*Project documentation.*
** A review of project documentation will be conducted to triangulate findings from interviews and questionnaires
^
2
^. This document review will follow the completion of questionnaires and interviews to address any information gaps rather than shaping materials iteratively. Key documents include project logs, meeting minutes, debrief notes and member participation profiles recorded using the ‘My Involvement Profile’ template created by ‘Shaping Our Lives’
^
26,
27
^. These documents, created at the beginning and throughout the PPIE project, provide further insights into the engagement process within the group and trials and help mitigate recall bias of interview participants
^
22
^.

This document review will provide insights into member expectations and how they have been met, trends in participation, and the impact of flexible methods such as online and in-person meetings, by examining attendance patterns and other data. Process measures (e.g. number and type of events conducted, number and impact of materials created) from project logs will also be reported. Meeting minutes which document group discussions and debrief notes, as reflective summaries of these conversations will help in understanding evolving engagement patterns. Additionally, we will review the end-of-year funding report provided to the sponsor to gain an overview of the project’s progress and outcomes.

Due to confidentiality reasons, as agreed upon by the members, meeting minutes and debrief notes will not be made publicly available. However, anonymised data, such as attendance percentages and overall project reports will be published.

